# Efficacy and mechanism of traditional Chinese medicine in relieving antibiotic-resistant bacterial diarrhea in children: study protocol for a randomized controlled trial

**DOI:** 10.1186/s13063-021-05381-8

**Published:** 2021-06-29

**Keywords:** Bacterial diarrhea, Traditional Chinese medicine, Antibiotic resistance, Clinical efficacy evaluation, Mechanism study

## Abstract

**Background:**

Bacterial infection is an important cause of diarrhea in children, potentially leading to malnutrition, growth and development disorders, and even death. Antibiotic abuse and resistance are widespread problems worldwide, especially in China. We therefore designed a study to evaluate the clinical efficacy and mechanism of traditional Chinese medicine in alleviating the effects of antibiotic resistance in childhood bacterial diarrhea and enhancing the sensitivity of pathogenic bacteria to antibiotics.

**Methods:**

This randomized, double-blind, placebo-controlled clinical trial has completed ChiCTR registration. The trial will randomly divide 120 children who meet the inclusion criteria into three groups: experimental group 1 (basic treatment + Gegen Qinlian decoction granules + Erbai drink placebo), experimental group 2 (basic treatment + Erbai drink granules + Gegen Qinlian decoction placebo), and control group (basic treatment + Gegen Qinlian decoction placebo + Erbai drink placebo). The main efficacy indicators will be antibiotic use rate and clinical cure rate, and the secondary efficacy indicators will be time to antibiotic intervention, effective rate, and course of treatment determined after 5 days. The following physical and chemical indicators will be measured: routine blood parameters, procalcitonin, C-reactive protein, electrocardiogram, liver and kidney function, electrolytes, routine urinalysis, routine stool analysis, and stool culture (including drug sensitivity).

**Discussion:**

The results of this study may provide an objective clinical basis for the use of traditional Chinese medicine in managing antibiotic-resistant bacterial diarrhea in children, formulating relevant guidelines, and demonstrating the use of traditional Chinese medicine for reducing the use of antibiotics.

**Trial registration:**

Chinese Clinical Trial Registry ChiCTR1900027915. Last refreshed on December 4, 2019.

## Background

Antibiotic abuse and drug resistance are widespread throughout the world, especially in China. The overuse of antibiotics has particularly important implications for children. Infectious diarrhea is one of the most common diseases worldwide, potentially causing malnutrition, growth and development disorders, and is the most common disease and the leading cause of death in children under the age of 5 years in developing countries. Studies [1] have reported that the detection rate of *Shigella flexneri* in stool specimens of children with diarrhea in economically backward areas is 64.95%, suggesting that bacterial infection was an important cause of infectious diarrhea in children. There is thus a need to evaluate the clinical efficacy and mechanism of traditional Chinese medicine in alleviating the resistance of childhood bacterial diarrhea to antibiotics and enhancing the antibiotic sensitivity of pathogenic bacteria.

Bacterial diarrhea in children is a common pediatric disease caused by a variety of pathogens. The common clinical symptoms are increased stool frequency and changes in stool characteristics. The distribution of pathogenic bacteria in children with bacterial diarrhea shows regional characteristics. Wang et al. [2] found that patients with bacterial diarrhea in Lanzhou were mainly infected with pathogenic *Escherichia coli* and *Shigella*, and Wang et al. [3] found that *Shigella* was the main pathogen responsible for bacterial diarrhea in children under 14 years of age in Xi'an from 2004 to 2016, though the detection rate of *Salmonella* gradually increased over time. Yuan et al. [4] showed that the pathogenic bacteria in children with bacterial diarrhea in Taiyuan from 2002 to 2007 were mainly *E. coli*, with the incidence of *Shigella* decreasing year by year. Cui et al. [5] collected 10,881 strains of various diarrhea pathogens in 16 provinces and cities in China, including seven genera, 22 strains, and 90 serotypes, including 7632 strains of *Shigella* (70.14%), 1351 strains of *Vibrio* (12.42%), 981 strains of *Salmonella* (9.02%), 341 strains (3.13%) of diarrheal *E. coli*, 302 strains (2.78%) of *Aeromonas*, 269 strains (2.47%) of *Pseudomonas*, and five strains (0.05%) of *Yersinia enterocolitica*.

Antibiotics are the most commonly used treatment for drug-resistant bacterial diarrhea, and the rigorous, reasonable, and scientific use of antibiotics can guarantee the successful control and treatment of drug-resistant bacterial diarrhea. However the widening and inappropriate use, and even abuse, of antibiotics has exacerbated the problem of drug resistance. Hou et al. [6] found that *E. coli* had a higher rate of resistance to ampicillin (98.5%), compound trimethoprim (77.0%), and ceftriaxone (63.0%) compared with *Shigella*, based on drug sensitivity tests. Li and Liang [7] found that the susceptibility rates of various bacterial genera to antibiotics differed, with greater sensitivity (> 90%) to fourth-generation cephalosporins The order of drug resistance was penicillins, aminoglycosides, sulfonamides, penicillin compound preparations, quinolones, and cephalosporins, and no bacteria were resistant to carbapenems. Zhao et al. [8] suggested that pathogens were most sensitive to third-generation cephalosporins, followed by fluoroquinolones and aminoglycosides, and were resistant to other antibiotics.

Pediatric drug-resistant bacterial diarrhea belongs to the category of damp-heat syndrome of diarrhea in traditional Chinese medicine (TCM). TCM has always advocated “differentiation and treatment,” which has advantages for the treatment of drug-resistant bacterial diarrhea in children. Wang et al. [9] used Gegen Qinlian decoction to treat patients with acute infectious diarrhea (intestinal damp-heat syndrome), with good safety results. The effects of this agent may be related to reductions in of plasma levels of C-reactive protein (CRP), interleukin-6, tumor necrosis factor-α, and endotoxin levels.

Given that bacterial diarrhea in children is a common and serious problem mainly caused by *Shigella* and *Salmonella*, antibiotics are frequently used as the main treatment option. However, their misuse and abuse have led to increasing drug resistance among pathogenic bacteria. Although some laboratory studies [10, 11] found that Gegen Qinlian decoction had a significant inhibitory effect on *Shigella* and *Salmonella*, information based on clinical trials in children is lacking.

Erbai drink is an empirical prescription used by the master of traditional Chinese medicine, Wang Lie. This prescription is used to treat diarrhea of damp-heat type in children. However, in the existing guidelines [12], the prescription for pediatric damp-heat diarrhea is Gegen Qinlian Decoction, But, in clinical application, the master of Chinese medicine Wang Lie found that Erbai drink also has a significant effect in the treatment of diarrhea in children with damp-heat type. Wang et al. [13] summarize Wang Lie’s experience and found that Erbai drink is “harmonizing spleen yin and yang, clearing heat, promoting diuresis and detoxifying,” which is used to treat diarrhea in children with damp heat.

Erbai drink granules: Radix Paeoniae Alba (Bai Shao) 10 g, Rhizoma Atractylodis Macrocephalae (Bai Zhu)10 g, Radix scutellariae (Huang Qin) 10 g, Semen Coicis (Yi Yiren ) 10 g, Rhizoma Atractylodis (Cang Zhu) 5 g, Semen Plantaginis (Che Qianzi)10 g; Gegen Qinlian decoction granules: Radix Puerariae lobatae (Ge Gen) 10 g, Radix Scutellariae (Huang Qin) 10 g, Rhizoma Coptidis (Huang Lian) 5 g, Radix Glycyrrhizae (Gan Cao) 5 g. Two Chinese medicine prescriptions can all clear away heat, eliminate dampness ,and stop diarrhea for children with damp-heat diarrhea, but it can be found from the composition of the medicine that Gegen Qinlian decoction has a better heat-clearing effect and Erbai drink has a better dampness-eliminating effect. So, we hope that this difference can be verified in actual clinical observations.

Therefore, it is necessary to implement clinical trials to determine the safety and efficacy of TCM (Gegen Qinlian decoction and Erbai drink) in the treatment of antibiotic-resistant bacterial diarrhea in children.

## Methods/design

### Study aim

We aim to use Erbai drink and Gegen Qinlian decoction combined with antibiotics as intervention methods to evaluate the clinical efficacy of TCM for the treatment of bacterial diarrhea in children. We will also formulate clinical programs and guidelines for the treatment of pediatric bacterial diarrhea using TCM, to provide clinical evidence for the use of TCM in reducing the use of antibiotics.Based on the evaluation of the clinical efficacy of the TCM preparations and their combined application, we aim to investigate the mechanism of TCM in alleviating antibiotic resistance and enhancing the sensitivity of pathogenic bacteria to antibiotics.We aim to monitor the incidence of clinical adverse events/reactions, general physical examination items, and laboratory parameters.

### Study design

This randomized, double-blind, placebo-controlled clinical trial will compare two different TCM preparations with a blank control group. The trial design is shown in Fig. 1.

**Fig. 1 Fig1:**
[figure not shown]
Study flow chart. Flow chart of enrolment, allocation, intervention, and assessment

### Setting and patients

A total of 120 children from the outpatient/inpatient departments of each participating center who meet the diagnostic criteria and inclusion criteria for bacterial diarrhea will be enrolled. The participating centers include the Children’s Diagnosis and Treatment Center of the Affiliated Hospital of Changchun University of Traditional Chinese Medicine, Shenzhen Children’s Hospital, and the First Affiliated Hospital of Hunan University of Traditional Chinese Medicine. The biological samples collected from the children must not be less than 2000. The children will be divided into three groups according to computer-generated random numbers, with a 1 in 3 probability of being allocated to any one group.

### Eligibility criteria

#### Diagnostic criteria

The Western medicine diagnostic criteria for drug-resistant bacterial diarrhea in children are as follows [14, 15]:
Resistant bacteria found in the stool culture.Prerequisites: stool characteristics changed, showing loose, watery, mucus, or pus-blooded stools. Course of the disease within 2 weeks.Auxiliary conditions: stool frequency higher than usual, and at least three times a day, with or without abdominal pain, vomiting, and abdominal distension.

The TCM diagnostic criteria for diarrhea in children with damp-heat syndrome are as follows [16]:
Main symptoms: watery stools, or like egg-drop soup, urgent diarrhea, frequent doses, and foul smell.Secondary symptoms: sometimes some mucus, abdominal pain, nausea and vomiting, or fever, irritability, thirst, yellow urine, red tongue, yellow and greasy coating, slippery pulse, purple hand venules.

#### Selection criteria

Age from 6 months to 14 years.Meet the Chinese and Western medicine diagnostic criteria, course of the disease within 2 weeks, and condition mild to moderate.White blood cell count in routine stool ≥ 5/high-power field (HPF), or increased procalcitonin, percentage of CRP or neutrophils, or total number of white blood cells in routine blood.Able to obtain consent from a guardian, fill in the informed consent form, and agree to participate (children > 8 years old should sign a consent form).

#### Exclusion criteria

Patients meeting any of the following criteria will be excluded:
Bacterial diarrhea caused by cholera, bacillary dysentery, typhoid fever, and paratyphoid fever (stool routine white blood cell count ≥ 15/HPF, and a few red blood cells).Children with severe dehydration, acidosis, shock, and immunodeficiency.Children with severe cardiovascular, liver, kidney, and hematopoietic diseases or with mental disorders.Acute diarrhea caused by intussusception and intestinal polyps.Diarrhea caused by surgery within 30 days before the clinical trial.Children who do not cooperate with treatment.Participated in other clinical trials within 1 month.Children with allergies to the known ingredients of the experimental drug.

#### Elimination criteria

Patients will be removed from the trial if they meet any of the following criteria:
After selection, the patient is found not to meet the selection criteria or to meet the exclusion criteria.Patients who fail to follow the protocol after selection.Patients with no post-treatment visit records after selection.

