#### Patient shedding criteria

Subjects with poor compliance during the trial, affecting the safety and efficacy evaluation.Subjects with serious adverse events, complications, or specific physiological changes, who are not suitable to continue the trial.Children for whom trial blindness is broken.Children who choose to withdraw from the trial.When combined drugs, especially the drugs that have a greater impact on the effectiveness and safety of the experimental drug.Cases who withdraw from the trial, are lost to follow-up, or who die for before completing treatment.Cases with insufficient data, affecting the evaluation of effectiveness and safety.

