One course of treatment for the above three groups will last 5 days, and one to two courses can be administered continuously. The specific observation time and related items are shown in Table 1.

**Table 1 Tab1:** Specific observation time and related items

Stage		Enrollment	Clinical observation time (days)									
**Date of visit**		**0**	**1**	**2**	**3**	**4**	**5**	**6**	**7**	**8**	**9**	**10**
**Case screening**		**√**										
**Sign informed consent**		**√**										
**Random entry group**		**√**										
**Delivery of test drugs**		**√**										
**CRF completed**		**√**	**√**	**√**	**√**	**√**	**√**	**√◎**	**√◎**	**√◎**	**√◎**	**√◎**
**Basic medical history**		**√**										
**General information**		**√**										
**General inspection items**	**Physical examination**	**√**	**√**	**√**	**√**		**√**	**√◎**	**√◎**	**√◎**	**√◎**	**√◎**
	**Routine blood test**	**√**	**◎**	**◎**	**√**	**◎**	**◎**	**√◎**	**√◎**	**√◎**	**√◎**	**√◎**
	**Procalcitonin**	**√**	**◎**	**◎**	**√**	**◎**	**√**	**◎**	**◎**	**◎**	**◎**	**◎**
	**C-reactive protein**	**√**	**◎**	**◎**		**◎**	**◎**	**√◎**	**√◎**	**√◎**	**√◎**	**√◎**
	**Electrocardiogram**	**√**					**√**	**√◎**	**√◎**	**√◎**	**√◎**	**√◎**
	**Liver and kidney function**	**√**					**√**	**√◎**	**√◎**	**√◎**	**√◎**	**√◎**
	**Electrolytes**	**√**					**√**					
	**Routine urine test**	**√**					**√**					
	**Routine stools**	**√**	**◎**	**◎**	**√**	**◎**	**√**	**√◎**	**√◎**	**√◎**	**√◎**	**√◎**
	**Stool culture (including drug sensitivity)**	**√**					**√**	**√◎**	**√◎**	**√◎**	**√◎**	**√◎**
**Stool characteristics**		**√**	**√**	**√**	**√**	**√**	**√**	**√◎**	**√◎**	**√◎**	**√◎**	**√◎**
**Stool frequency**		**√**	**√**	**√**	**√**	**√**	**√**	**√◎**	**√◎**	**√◎**	**√◎**	**√◎**
**Symptom evaluation**		**√**	**√**	**√**	**√**	**√**	**√**	**√◎**	**√◎**	**√◎**	**√◎**	**√◎**
**Temperature card**		**√**	**√**	**√**	**√**	**√**	**√**	**√◎**	**√◎**	**√◎**	**√◎**	**√◎**

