### Outcome assessment

#### Primary outcome measures

Antibiotic use rate and clinical cure rate

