### Statistical analysis

Statistical analysis will be carried out using SAS 9.4 or above. According to the data characteristics, measured data will be analyzed by independent sample *t* tests or rank sum tests for comparison between groups and numerical data will be analyzed by χ^2^or Fisher’s exact probability tests. Laboratory data for all clinical endpoints will be analyzed according to intention to treat (ITT) and compliance (PP) analyses, and safety analysis will be performed using a safety data set (SS). The efficacy scores at the time of patient enrollment, intermediate follow-up (day 3, day 4 to day 7 after treatment), and at the end point of the trial will be calculated, and the mean, standard deviation, median, P5, P75, maximum and minimum values of the differences in values between baseline and the treatment period will be used. PP and ITT will be adopted to analyze the main index and overall index. Subjects with positive urine culture indicators will be included in the statistical subgroup to analyze the correlation between the study program and the overall efficacy evaluation index. Because this is a multicenter, randomized, double-blind controlled trial, the possible central effect on efficacy indicators should be considered.

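### Randomised children can be removed or shed for events after randomisation, and nothing keeps them or their outcomes in the promised ITT analysis

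*Protocol article*

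**What the plan says.** Table 1 places randomisation ("Random entry group") on day 0, in the enrolment column. Three sets of rules then apply.

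- **Elimination criteria.** "Patients will be removed from the trial if they meet any of the following criteria". The list covers children later found ineligible, "Patients who fail to follow the protocol after selection", and "Patients with no post-treatment visit records after selection".
- **Patient shedding criteria.** These cover poor compliance, serious adverse events or complications in children not suitable to continue, a broken blind, withdrawal, loss to follow-up and death. They also include "When combined drugs, especially the drugs that have a greater impact on the effectiveness and safety of the experimental drug" and "Cases with insufficient data, affecting the evaluation of effectiveness and safety".
- **Note to Table 1.** Main symptoms and signs are recorded until the child leaves the group. Stool tests, stool culture and safety tests are reviewed at that point.

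The primary outcomes are "Antibiotic use rate and clinical cure rate". For the analysis, the article says "PP and ITT will be adopted to analyze the main index and overall index". It does not say how a removed or shed child is treated in either set. The Test drugs section allows ceftriaxone to be added during the illness.

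**The concern.** Most of these reasons arise after randomisation and can depend on how the child is doing: worsening, intolerance, stopping the granules, extra medication, incomplete records. If treatment affects any of them, the children who remain in each arm are no longer comparable, and randomisation does not protect the comparison of antibiotic use or cure. An ITT analysis guards against this only if removed children stay in the set and their outcomes are known. The article secures neither.

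The second part matters most. An analysis plan written later can define ITT correctly, but it cannot recover antibiotic use or cure that nobody recorded after the child left.

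One criterion also touches a primary endpoint. An antibiotic given for bacterial diarrhoea fits the description of a combined drug with a large effect on the assessment of efficacy, and no exemption is written. The trial runs in three centres, which could apply the wording differently.

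**Working it through.** **1. The plan's own figures (Sample size section).** Inputs: antibiotic use 46% in the TCM groups and 80% in control; α = 0.05, taken as two-sided; the stated β = 0.80 read as power 0.80.

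- Without continuity correction: n = [1.960·√(2·0.63·0.37) + 0.842·√(0.46·0.54 + 0.80·0.20)]² / 0.34² = (1.338 + 0.538)² / 0.1156 = 30.4, so 31 per group.
- With continuity correction: n' = (n/4)·[1 + √(1 + 4/(n·0.34))]² = (30.4/4)·(1 + 1.177)² ≈ 36.1, so 37 per group.

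The stated 37 reproduces. The plan enrols 120, or 40 per arm, and allows for 10% drop-out. That is 4 per arm, leaving 36.

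**2. What selective loss of that size can do.** The documents give no removal rates by outcome, so this is illustration. Assume no treatment effect and 60% antibiotic use in both arms (24/40), with 4 children lost per arm.

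| Lost from arm A | Lost from arm B | Rate in A | Rate in B | False gap |
|---|---|---|---|---|
| 4 users | 4 non-users | 20/36 = 55.6% | 24/36 = 66.7% | 11.1 points |
| 3 users, 1 non-user | 1 user, 3 non-users | 21/36 = 58.3% | 23/36 = 63.9% | 5.6 points |
| in proportion (2.4 users, 1.6 non-users) | in proportion | 21.6/36 = 60% | 21.6/36 = 60% | 0 |

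The first row is the extreme for this amount of loss: the gap is 4/36 whatever common rate is assumed, provided each arm holds at least 4 users and 4 non-users. For scale, 11.1/34 is about one third of the planned difference. On its own it would not be significant: pooled rate 44/72 = 0.611, SE = √(0.611·0.389·2/36) = 0.115, z = 0.111/0.115 ≈ 0.97, p ≈ 0.33.

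**3. If the combined-drugs criterion were applied to some antibiotic users.** Let a share f of users be shed. The observed rate is then p(1−f) / [(1−p) + p(1−f)].

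- Same f in every arm, at the planning rates: f = 20% gives 76.2% v 40.5% (gap 35.7 points); f = 50% gives 66.7% v 29.9% (gap 36.8 points). The gap stays close to 34 points, but both rates are understated and power falls from 89.8% to 87.2% and 79.0% (pooled variance, no continuity correction).
- Users shed in one arm only, true use 80% in both arms: the false gap is 3.8 points at f = 20% and 13.3 points at f = 50%.

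**4. Is shedding of all users intended?** Expected users at the planning rates: 0.80·40 = 32 in control and 0.46·40 = 18.4 in each TCM arm, so 68.8 of 120, or 57%. That cannot be squared with a 10% drop-out allowance.

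**The case against.** The strongest reply is that removal from the trial is not removal from the analysis. ITT ordinarily means all randomised children, compliance rules ordinarily define PP, and exact set definitions are commonly left to an analysis plan that is not shown. Much of this stands: a reader might infer that the article flatly contradicts its ITT promise, but it never says that ITT is formed after the removals. What the reply does not meet is the data-collection rule. If recording ends when a child leaves, a correct ITT definition has gaps where the outcomes should be.

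A reader might also infer that every child given ceftriaxone is to be shed. The documents do not support that. The Test drugs section permits the drug, the Study aim speaks of TCM together with antibiotics, its use is a primary outcome, and step 4 shows the loss would far exceed the planned drop-out. What remains is an unwritten exemption that centres could read differently.

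Three smaller limits also stand. The article says both PP and ITT will be used, which does not establish equal rank. The elimination rule concerns children with no post-treatment record at all, not those who miss single visits, although the shedding list adds insufficient data. And the trial is described as double-blind, which limits removal steered by knowledge of the arm. Blinding does not prevent imbalance that arises because treatment changes worsening, tolerance or compliance.

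**Conclusion.** The point holds in this form: the removal and shedding rules act after randomisation, recording of symptoms stops when a child leaves, and nothing in the article keeps these children or their outcomes in the ITT set. Both primary comparisons are therefore open to selection bias. The combined-drugs criterion also needs to be reconciled with the antibiotic endpoint.

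The size is unknown, because no removal rates are given. With the planned 4 losses per arm, the false gap in antibiotic use lies between 0 and 11 points depending on how selective the losses are. The 11-point figure is a hypothetical extreme under an assumed common rate, not a forecast, and would not by itself produce a significant result. Larger losses, or uneven use of the combined-drugs criterion, could exceed it.

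**What to change.** - State that the primary analysis is ITT in all randomised children, analysed as allocated, and that PP is supportive.
- Let the Elimination criteria and Patient shedding criteria decide only who belongs to the PP set.
- For children who stop test drug and have not withdrawn consent, keep recording antibiotic use and cure at the visits already in Table 1, including those of a second course where one is given. Amend the note to Table 1 to match.
- Add a sensitivity analysis for unknown outcomes under opposite assumptions: once counted as antibiotic used and not cured, once as the reverse.
- Reconcile the combined-drugs criterion with the Study aim, Test drugs and Primary outcome measures sections, so that all centres apply it alike.

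The cost is a wording change, some extra data collection on an existing schedule, and a slightly diluted effect estimate because children who stopped the granules are included. Retention also helps precision: at the planning rates, power is 89.8% with 40 per arm against 86.4% with 36 (pooled variance, no continuity correction), before any dilution. The article reports that recruitment was under way, so the data-collection change is the urgent part.
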